### Expected results

We expect to obtain the following results:
•Identification of the mortality rate at 30 days (30-day mortality rate), divided according to the different type of intervention (ICD-9-CM classification) and stratified for 5-years age group;•Identification of the general morbidity index at 30 days (30-day morbidity rate), divided according to the different type of intervention (ICD-9-CM classification) and stratified for 10-years age group;•Identification of mean length of hospital stay (LOS), in days, according to the different surgical procedure group (ICD-9-CM classification);•Sensitivity and specificity of the following scores:
- Charlson Age Comorbidity Index (CACI)- Cohomprensive Complication Index- Simplified Acute Physiology Score II (SAPSII)- American College of Surgeons National Surgical Quality Improvement Program (ACS NSQIP)surgical risk calculator- Calculation of postOperative Risk in Emergency Surgery (CORES)- Surgical Mortality Probability Model (SMPM)•Evaluation of the prevalence of emergency surgery in different age groups by geographic area (Emergency surgery per 100.000 inhabitants);•Identification of an Elderly / Non Elderly ratio;•Evaluation of the use of the following scores in elderly patients:
- Frailty Fried Index- Canadian Study of Health and Aging (CSHA) frailty score- Emergency Surgery Frailty Index (EmSFI)- Urgent Surgery Elderly Mortality (USEM) score- 5 modified Frailty Index (5-mFI)

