### Outcome measures

The primary outcomes are 30-day overall postoperative morbidity and mortality rates. Secondary outcomes are 30-day postoperative morbidity and mortality rates, stratified for each procedure or cause of intervention, length of hospital stay, admission and length of stay in ICU, and place of discharge (home or rehabilitation or care facility). Severity of every disease will be assessed according to the AAST EGS score (29). Other secondary outcomes include the number of elderly subjects undergoing yearly emergency surgery, reported as the elderly to non-elderly patient ratio, emergency surgery in the elderly per 100,000 inhabitants, frequency of use of frailty score. Elderly are define as any patient >65 years old according to the World Health Organization. Moreover, the study will evaluate the sensitivity and specificity of the following scores: Charlson Age Comorbidity Index (CACI), Simplified Acute Physiology Score II (SAPSII), American College of Surgeons National Surgical Quality Improvement Program (ACS NSQIP), Calculation of Postoperative Risk in Emergency Surgery (CORES), Surgical Mortality Probability Model (SMPM), Urgent Surgery Elderly Mortality (USEM) score, Emergency Surgery Frailty index (EmSFI), 5 modified Frailty Index (5-mFI). The postoperative complications are reported and categorized according to the Clavien-Dindo classification system. Morbidity we will be assessed by detecting all adverse event according “Common terminology criteria for adverse events version 5” (30). Therefore, the Comprehensive Complication Index will be calculated (31).

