	Onset symptoms	Obstruction, acute abdomen (peritonitis—abscess and/or overt perforations), Vascular disorders, Trauma
	Primary operative indication	Benign/malignant/delayed elective
	Surgical approach	Open/Laparoscopic/Laparoscopic converted/Laparoscopic assisted
	Primary surgical procedure	ICD-9-CM code
	Associated procedures	Numbers
	List of associated procedures	ICD-9-CM code
	Intraoperative reliefs	Blood loss (ml), peritoneal contamination (yes/no)
	Operative time	Minutes
	ICU admission	Yes/no
	ICU length of stay	Dayes
Follow-ups	Date of discharge	Day/month/year
	Total length of stay	Days
	Type of discharge	Home, short-term rehabilitation facility, caregiver residential facility
	Complications 30-daypostoperatively	Yes/no
	Complication type	Free text
	Complication grade (Clavien-Dindo classification)	None/I/II/III/IV/V
	30-day mortality	Yes/no
Score		ASA, CACI, SAPSII, ACS-NSQIP, CORES, SMPM, USEM, EmSFI, 5-mFI

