### Statistical analysis

The report of this study will be prepared in accordance with guidelines set by the STROBE (Strengthening the Reporting of Observational Studies in Epidemiology) statement for observational studies (30). Statistical analysis will be performed either with SPSS software, version 21 to 26 (IBM Corp. Released 2020. IBM SPSS Statistics for MacOsx, Version 27.0. Armonk, NY: IBM Corp) for MacOSX or StataCorp2019 STATA Statistical Software: release 16 (College Station,TX: StataCorp LLC). First, data normality will be tested using the Shapiro–Wilk test or Kolmogorov– Smirnov test. Dichotomous data and counts will be presented in frequencies. Continuous data will be presented as mean values plus standard deviations, or as median values and interquartile ranges. The 95% confidence interval will always be reported where appropriate. Differences between means will be compared using the independent sample Student's *t* test, the pairwise comparison Student's *t* test, the Mann–Whitney *U* test, the Kruskal–Wallis test or other analysis of variance (ANOVA) tests. Differences between medians will be compared using the Kolmogorov–Smirnov test or special application of the Pearson chi square test by using the median as cut-off. To compare differences in frequencies, Fisher's exact test or *χ*^2^ test, with or without Yates correction will be performed. Receiver operating characteristic (ROC) curve analysis will be performed to estimate sensitivity and specificity of each score. Linear correlation will be assessed by Pearson's or Spearman's test, if needed. Multivariate analyses will be performed using logistic regression models that consider mortality and morbidity as dependent variables. A *P* value of <0.05 will be considered statistically significant.

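### The Comprehensive Complication Index, a summary of the outcome, is listed among the scores whose sensitivity and specificity will be estimated

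*Protocol article*

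**What the plan says.** The Expected results section promises "Sensitivity and specificity of the following scores" and then lists six items. The list opens with "Charlson Age Comorbidity Index (CACI)- Cohomprensive Complication Index", so its second item is the Comprehensive Complication Index (misspelled), placed between the risk scores CACI and SAPSII. The other three are ACS NSQIP, CORES and SMPM.

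The Statistical analysis section gives the method: "Receiver operating characteristic (ROC) curve analysis will be performed to estimate sensitivity and specificity of each score".

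The Outcome measures section gives the index a different role. It states that "The primary outcomes are 30-day overall postoperative morbidity and mortality rates" and that "The postoperative complications are reported and categorized according to the Clavien-Dindo classification system". After adding that adverse events are detected with CTCAE version 5, it concludes: "Therefore, the Comprehensive Complication Index will be calculated (31". The same section has its own list of eight scores to be evaluated for sensitivity and specificity: CACI, SAPSII, ACS NSQIP, CORES, SMPM, USEM, EmSFI and 5-mFI. The index is not among them.

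The Score row of Table 1 holds ASA and those same eight scores, again without the index. Under Follow-ups, Table 1 has a yes/no field for 30-day complications, a free-text complication type, and a field named "Complication grade (Clavien-Dindo classification" with options None, I, II, III, IV and V.

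**The concern.** A prognostic score should be known before the outcome it is meant to predict. Outcome measures calculates this index from the complications themselves, so it exists only after they have occurred and re-expresses the morbidity outcome on a numerical scale. Estimating its sensitivity and specificity for 30-day morbidity compares the outcome with itself.

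The Objectives section makes the prognostic role of existing risk scores, and the choice of the most suitable one, a secondary endpoint. Putting an outcome summary into that comparison adds an entry with near-perfect apparent accuracy that cannot help anyone decide before surgery. The sections also disagree on which scores are to be evaluated, and the text does not say which list governs.

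**Working it through.** The protocol gives no accuracy figure to reproduce. The check is a comparison of the sections followed by a short derivation.

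**1. The three lists.**

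| Place | Scores | Index included? |
|---|---|---|
| Outcome measures, sensitivity/specificity list | CACI, SAPSII, ACS NSQIP, CORES, SMPM, USEM, EmSFI, 5-mFI (8) | No |
| Table 1, Score row | ASA plus the same 8 (9) | No |
| Expected results, sensitivity/specificity list | CACI, the index, SAPSII, ACS NSQIP, CORES, SMPM (6) | Yes |

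Removing the index from the third list leaves 6 − 1 = 5 scores, all of which appear in the other two. The remaining 8 − 5 = 3 scores in Outcome measures (USEM, EmSFI, 5-mFI) appear in Expected results under a separate item on the use of scores in elderly patients.

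**2. The reference outcome.** Expected results does not name one. Statistical analysis takes mortality and morbidity as the dependent variables of the regression models, and the Discussion speaks of scores predicting the outcomes of emergency surgery. Thirty-day morbidity and mortality are therefore the natural reading.

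**3. Accuracy for morbidity.** Let Y = 1 if any complication is recorded within 30 days and 0 otherwise, and let I be the index. Assume that I = 0 when there is no complication and I > 0 when there is at least one. At the cut-off I > 0:

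- sensitivity = P(I > 0 | Y = 1) = 1
- specificity = P(I = 0 | Y = 0) = 1
- AUC = P(I of a case > I of a non-case) = 1

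Neither the weights nor the event rates enter.

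**4. Accuracy for mortality.** If grade V denotes death and gives the largest value of the index, every death ranks above every survivor and the AUC is again 1. The document does not spell out the meaning of grade V, so this step is conditional.

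**5. Numerical illustration.** I used 5,000 simulated patients per scenario, with morbidity 20%, 35% or 50%, mortality 2%, 5% or 15%, and two arbitrary increasing weightings of the grades: 3 × 3 × 2 = 18 scenarios. All of these inputs are assumptions. The index had AUC 1.000 for morbidity (sensitivity and specificity 100% at I > 0) and AUC 1.000 for mortality in all 18. A pure-noise score had AUC between 0.49 and 0.52 for morbidity. The simulation builds in the assumptions of steps 3 and 4, so it illustrates the derivation and is not independent evidence.

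**6. The data field.** Outcome measures foresees detection of all adverse events, whereas Table 1 displays one grade field without sub-grades and no visible repeat entry. An index meant to summarise all of a patient's complications needs the grade of each. The table neither confirms nor rules out that these are captured.

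**The case against.** The strongest reply is that this is a misplaced list item in a loosely written section. Outcome measures states which scores will be evaluated and leaves the index out, as does the Score row of Table 1. Objectives speaks of risk scores, and Statistical analysis does not name the index. Expected results also names the Fried and CSHA frailty measures, which appear in neither of the other lists. An analyst working from the other sections would not enter the index. This stands in part: the correct list is already in the document and the effect is confined to one secondary analysis. It does not remove the contradiction, because no sentence gives one section precedence.

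A reader might go further and infer that the index will win the comparison and be reported as the best score. The documents do not support that. It would require the analysts to prefer Expected results to Outcome measures and then to accept a perfect AUC for a postoperative quantity without question. No reference outcome is named either. Against other outcomes in Outcome measures, such as ICU admission or place of discharge, accuracy would not be perfect by definition.

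A reader might also infer from Table 1 that only one collapsed grade is stored per patient, so that the index cannot be computed. A condensed table of fields and options does not establish that. Nor can the size of any resulting error be given, since the document does not state the index's weights.

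**Conclusion.** The point holds as an internal contradiction with a circular analysis as its consequence. If Expected results is followed, the index's sensitivity, specificity and AUC for 30-day morbidity are 100%, 100% and 1 by construction, assuming only that the index is zero exactly when no complication is recorded. For mortality the AUC is also 1 if grade V denotes death and carries the maximum value. These figures would say nothing about prediction and would distort the secondary search for the most suitable scoring system.

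The reach is limited. The 30-day morbidity and mortality rates and the accuracy estimates of the other scores do not change. This is a correction to one list, not a flaw in the design. The Table 1 point is secondary and remains a question for the sponsor.

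**What to change.** 1. In Expected results, delete the Comprehensive Complication Index from the sensitivity and specificity list, leaving CACI, SAPSII, ACS NSQIP, CORES and SMPM.
2. Reconcile that list with Outcome measures, including whether USEM, EmSFI and 5-mFI are to be assessed for accuracy or only for their use in elderly patients.
3. State that the index serves only as an outcome measure.
4. Confirm that the grade of every complication within 30 days is captured before the index is calculated. If it is not, report the Clavien-Dindo grade instead.

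Items 1 to 3 cost only protocol wording. Item 4 costs one query to the data coordination centre. If event-level grades turn out to be missing, recovering them could be expensive, because the Study time-line has main data collection starting on 1 September 2021 and charts might have to be re-read at every site. Reporting the grade alone avoids that cost.

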
## Protocol

### Objectives

The primary endpoint of this Italian nationwide study is to analyze the clinicopathological findings, management strategies and short-term outcomes of gastrointestinal emergency procedures performed in patients over 18. Secondary endpoints will be to evaluate to analyze the prognostic role of existing risk-scores to define the most suitable scoring system for gastro-intestinal surgical emergency. We will conduct an epidemiological investigation to gather information about the number of patients operated on yearly, and the prevalence of various pathological conditions leading patients to need emergency surgery. Furthermore, we aim to identify any specific parameters that may be used as variables for new scoring system, peri-operative variables predicting adverse results and any critical issues in the management of these patients.

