### Study design and participating sites

The prospective, observational study will be conducted following a resident-led model, similar to what has been described by Banghu et al. and van Rossem et al. and the SPIRIT guidelines (23–25). Briefly, teams of medical students and surgical residents with senior staff surgeon oversight collect data on patients across Italy for 18 months. The Data Coordination Center (DCC) is the Colorectal Surgery Unit of Surgery Centre, – Fondazione Campus Bio-Medico University Hospital, University Campus Bio-Medico of Rome, Italy and the Study Director is responsible for the selection of the study sites. Any center performing emergency surgery can participate in this trial. The centers include academic medical centers, teaching hospitals, tertiary referral centers and community hospitals. Although this study protocol is similar to what adopted in previous research (26), in order to ensure that there is a uniformity of data acquisition, centers which do not participated in such previous study performed a 3-month pilot study collecting data retrospectively. All the data taken refers to the time of access of the patient in the emergency room or in any case to the first data available before any procedure. Such data are not published, and are stored separately for possible further analyses. All patients are treated according to the local hospital protocol and receive routine care as standard therapy. Whenever possible, patients with intestinal obstruction are treated according to SICUT Delphi consensus statements (27). The duration of the recruitment phase of patients is expected to be 18 months. The main strength of this project is the multicenter, prospective, contemporary methodology, with independent validation of data. This will produce high quality data on the emergency procedures carried out for gastro-intestinal emergency and on outcomes throughout Italy from a wide range of hospital types. Limitations include the inability to assess the postoperative visits to the general practitioner. Moreover, a minority of patients may present to other hospitals with complications following surgery, or because they need medical assessment. Despite this, teams will try to document the number of patients that were readmitted to other facilities. Our study uses the standard 30-day follow-up period, as this is the international standard and allows comparison to other studies. However, complications which may occur after 90 days will be reported as completely as possible.

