### Study time-line

The following timeline has been outlined, to define specific stages of the study:
•May 13–June 30, 2021: invitation to satellite centers to participate.•1 July–31 August, 2021: pilot study and standardization of data collection.•1 September 2021–31 August, 2022: main data collection.•1 September 2022–28 February, 2023: data collection on specific topics.•1 March–30 June, 2023: completion of the collection of any missing data.•1 July–31 December 2023: “interim analysis” of complete data excluding follow-up•February 28, 2025: study completion for last potential follow-up.

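### Emergency surgery per 100,000 inhabitants, overall, in the elderly and by area, cannot be validly estimated from an invited, selected set of centres with no recorded residence or coverage

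*Protocol article*

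**What the plan says.** Three sections of the protocol article commit to population figures. Objectives sets out to "gather information about the number of patients operated on yearly, and the prevalence of various pathological conditions leading patients to need emergency surgery". Outcome measures lists, among the other secondary outcomes, "emergency surgery in the elderly per 100,000 inhabitants, frequency of use of frailty score". Expected results extends this to all age groups and to areas: "Evaluation of the prevalence of emergency surgery in different age groups by geographic area (Emergency surgery per 100.000 inhabitants").

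On who contributes data, Study design and participating sites says "Any center performing emergency surgery can participate in this trial" and also that "the Study Director is responsible for the selection of the study sites". Study time-line opens with "invitation to satellite centers to participate". Exclusion criteria remove patients without informed consent and those in another trial. Data collection, validation, and management admits to the pooled analysis only datasets more than 95% complete.

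Table 1 has a centre number but no field for the patient's residence or region. Privacy says the general database will conceal which centre sent the data.

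On time, Study design gives 18 months of recruitment. Study time-line has 12 months of main collection (1 September 2021 to 31 August 2022), then six months to 28 February 2023 described as "data collection on specific topics".

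**The concern.** A rate per 100,000 inhabitants has a numerator and a denominator that must refer to the same people: all eligible procedures among the inhabitants counted below the line. The design supplies neither side. Procedures at hospitals that do not take part are never seen, and some procedures at participating hospitals are removed by the consent, other-trial and completeness rules. No population is named that the participating centres serve.

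If the captured cases are divided by resident population, the result mixes the true rate with the share of activity that joined the study. A comparison between areas then partly compares participation. A reader of a nationwide study could take such figures as real regional differences in disease or in access to surgery.

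The yearly count has a further difficulty. The article does not say which window it rests on, or whether the last six months enrol all comers.

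**Working it through.** The article states no number of centres, coverage or expected rate, so there is no planned figure to reproduce. The check is an identity, and every coverage, retention and inflow value below is an assumption.

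**1. Rate over resident population**

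Let s be the share of the area's eligible procedures done in participating centres, and r the share of those kept after the consent, other-trial and completeness rules. Then c = s × r, observed rate = true rate × c, and relative shortfall = 1 − c. With the true rate indexed at 100:

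| s | observed, r = 1.0 | observed, r = 0.8 |
|---|---|---|
| 0.10 | 10 | 8 |
| 0.30 | 30 | 24 |
| 0.50 | 50 | 40 |
| 0.70 | 70 | 56 |
| 0.90 | 90 | 72 |
| 1.00 | 100 | 80 |

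Even with every hospital taking part, retention of 80% to 90% gives 80% to 90% of the true rate.

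**2. Comparison of two areas with the same true rate**

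The observed ratio equals the ratio of coverages:
- coverage 60% and 20%: 0.60 / 0.20 = 3.0
- coverage 50% and 25%: 0.50 / 0.25 = 2.0
- coverage 40% and 30%: 0.40 / 0.30 = 1.33

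**3. Direction in a single area**

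Suppose cases are assigned by the hospital's location because residence is not recorded. Let f be the number of non-resident procedures relative to those of residents. Then observed / true = c × (1 + f).
- c = 0.50, f = 0.2 to 0.3: 0.50 × 1.2 = 0.60 to 0.50 × 1.3 = 0.65
- c = 0.90, f = 0.2 to 0.3: 0.90 × 1.2 = 1.08 to 0.90 × 1.3 = 1.17

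The sign changes at f = 1/c − 1, which for c = 0.90 is 0.11. A downward bias is therefore not assured for every area.

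**4. Elderly to non-elderly ratio**

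This ratio needs no population denominator. It is distorted only by the ratio of capture in the two age groups: none if capture is equal, 0.40 / 0.50 = 0.80 if the elderly are captured less, and 0.50 / 0.40 = 1.25 if they are captured more.

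**5. What the article offers as a remedy**

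The check for missed patients in Data collection, validation, and management uses admission diagnoses and procedures within each centre. It can raise r but cannot change s. The limitations listed in Study design concern follow-up contacts elsewhere and do not mention incomplete coverage.

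**The case against.** The strongest reply is that little depends on this. The primary outcomes are 30-day morbidity and mortality, and the main secondary outcomes (stratified rates, stay, intensive care, discharge, accuracy of scores) need no population denominator. The per-100,000 rate is one clause and one bullet, and it can be dropped or relabelled without touching enrolment. That stands, and it lowers the priority.

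A second reply is that a catchment definition may sit in the full protocol or the SAP. A denominator could indeed be defined there. It would not recover procedures at hospitals that never joined, nor a residence field absent from the data dictionary as printed. Coverage could only come from outside data.

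Third, Table 1 records a centre number, so grouping by hospital area is possible in principle. That locates the hospital and not the inhabitant, and it sits uneasily with the promise of centre anonymity. The query loop, the missed-patient check and the four months for completing missing data do reduce loss within centres. Having no minimum number of patients helps coverage by letting small hospitals join.

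Two stronger readings are tempting:
- A reader might infer that the rate must always be too low. That holds over the resident population as a whole, but not for one well-covered area with referral inflow.
- A reader might infer that 18 months will be treated as one year, or that the last six months are a topic-selected sample. No section says the former. On the latter, the time-line may equally mean extra topic data on all comers. A second autumn and winter would unbalance the seasonal mix, but those are different months, each observed once.

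**Conclusion.** The concern holds. As designed, the study cannot validly estimate emergency surgery per 100,000 inhabitants, whether overall, in the elderly or by area. Over resident population the rate is understated by the uncaptured share, 1 − c, and differences between areas partly reflect participation. The documents do not allow that share to be computed. The tabulated values only illustrate the identity and do not measure the error in this study.

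The conclusion assumes that not every hospital in an area takes part, or that some eligible patients are lost to the exclusions, and that no outside data supply coverage or residence. It does not extend to the primary outcomes. The elderly to non-elderly ratio remains usable as a description of the participating centres. This should be fixed before results are reported, but it is not a threat to the study as a whole.

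The time base is a separate point of clarity. The article leaves open which months feed the yearly counts, and no size of error can be attached to that from the text.

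**What to change.** In Outcome measures and Expected results, choose one of the following:
- Remove the per-100,000 and geographic prevalence results.
- Restrict them to areas where all hospitals participate and patient residence is known.
- Take the numerator from official hospital discharge data.

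If none of these is adopted, report case mix and the elderly to non-elderly ratio, stated as describing participating centres only.

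Separately, reconcile the 18-month recruitment in Study design with the two periods in Study time-line, and state whether the last six months enrol all comers. Base yearly counts on the 12-month main window. Add the last six months only if they do enrol all comers, and then state the person-time used.

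Removing or relabelling the rates costs protocol and SAP wording and one set of descriptive figures. Keeping a population rate costs more: residence data and proof of full coverage, or access to discharge data. Neither route changes enrolment criteria or the primary analysis.
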